### **3.2 Phase 2: Qualitative Study-Structured One-On-One Interviews (Participants' Psychological Well-being, Experiences, and Perspectives)**

During the third phase of our research, we aim to qualitatively investigate the perspectives and experiences of adults with KOA who have undergone a 12-week intervention involving HILT with exercise, in comparison to those who received placebo laser therapy with exercise.

#### **3.2.1 Procedures**

To accomplish this goal, the study will conduct individual interviews either in person or online, using a structured research questionnaire. We will arrange suitable physical or online meeting locations, ensuring participants' comfort with their chosen method. The interviews will be conducted on a one-on-one basis with selected participants, and each interview will be audio or video-recorded with participants' consent. A trained interviewer, knowledgeable about the study's objectives but maintaining neutrality to prevent bias, will administer the interviews. Questions will be posed in a conversational manner, allowing participants to elaborate on their experiences and perspectives. Comprehensive notes, capturing both verbal responses and non-verbal cues, will be taken during the interviews.

#### **3.2.2 Sampling method**

Total of 10 participants from each group will be randomly selected using a computer-generated list to mitigate any potential selection bias. The sampling process will be performed by the principal investigator, who will not be involved in the intervention and outcome assessment. Sampling will continue until thematic saturation is reached, ensuring comprehensive coverage of the research topic.

### 3.2.3 Outcomes Measures

The outcomes of interest include participants' psychological well-being, experiences, and perspectives throughout the 12-week intervention involving HILT with exercise or placebo laser therapy with exercise. These outcomes will be explored through structured one-on-one interview, which allowing participants to share their subjective experiences and perceptions. The interview script is generated based on WHO-5 Well-Being Index and SF-36.

1. WHO-5 Well-Being Index: Developed by the World Health Organization, this index assesses overall psychological well-being by querying mood, vitality, and general well-being. The WHO-5 demonstrates strong internal consistency (Cronbach's alpha coefficient of 0.858) and convergent validity where the significant correlations with PHQ-9, HADS-anxiety, and HADS-depression (Maroufizadeh et al., 2019). Please refer to the Appendix 2.
2. Short Form 36 Health Survey (SF-36): Widely used to assess health-related quality of life, SF-36 provides valuable insights into psychological well-being. Despite being primarily designed for health-related quality of life, SF-36's total scores exhibit high responsiveness ( $>0.9$  effect sizes) (Clement et al., 2022). Thresholds of  $\leq 52$  in the MH subscale and  $\leq 56$  in the SF-36 effectively detect anxiety and depression, with additional reliable thresholds ( $\leq 35$  and  $\leq 40$  in MCS scores) for identifying these conditions (Matcham et al., 2016). Please refer to the Appendix 3.

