
included in this phase, which examines knee pain, physical function, and psychological health. Phase 3 on the other hand, emphasises the qualitative aspect and demonstrates the method to carry out structured one-on-one interviews with participants to discover more about their points of view, experiences, and feelings expressed. Phase 1 is significant due to the fact that it offers an in-depth examination of the combined intervention's short-term effects. It provides immediate data regarding how it affects physical function, psychological health, and knee pain. Phase 2 extends this inquiry, emphasising the long-term effects over a 12-weeks follow-up period, resulting in valuable data on sustained improvements. Phase 3 captures the experiences and perspectives of the patients, providing a deeper significance to the overall findings through qualitative investigation through structured interviews. Therefore, the combination of exercise and high intensity laser therapy, with an emphasis on holistic well-being and long-term effects, has the potential to reverse the damage caused by knee osteoarthritis. This will also provide a comprehensive comprehension of the effects of treatment and patient experiences, which will improve global management strategies.

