#### **1.4.2 Specific Objectives**

- 1) To examine the short-and long-term effects of HILT combined with rehabilitation exercise on knee pain, physical function and knee-related disability in adults with mild to moderate KOA.
- 2) To examine the potential disease-modifying effects of high-intensity laser therapy in combination with rehabilitation exercise in improving knee joint structure in adults with early knee osteoarthritis.

- 3) To evaluate patient-centered outcomes, including the impact on daily activities, quality of life, and overall patient satisfaction, to gain a more holistic perspective on the effectiveness of the combined intervention.

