### **1.5 Research Hypothesis**

- 1) Combining high-intensity laser therapy with rehabilitation exercise will significantly reduce knee pain, improve physical function, and reduce knee-related disability levels among adults with early knee osteoarthritis in the long term.
- 2) Combining high-intensity laser therapy with rehabilitation exercise will report positive lived experiences and perceptions. These experiences will significantly contribute to improved daily functioning, enhanced quality of life, and overall patient satisfaction compared to those in the control group.
- 3) Combining HILT with rehabilitation exercise will report positive lived experiences and perceptions. These experiences will significantly contribute to improved daily functioning, enhanced quality of life, and overall patient satisfaction compared to those in the control group.

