### Scoring:

The raw score is calculated by totaling the figures of the five answers. The raw score ranges from 0 to 25, 0 representing worst possible and 25 representing best possible quality of life.

To obtain a percentage score ranging from 0 to 100, the raw score is multiplied by 4. A percentage score of 0 represents worst possible, whereas a score of 100 represents best possible quality of life.

Regional Office for Europe WHO. Use of Well-Being Measures in Primary Health Care - The DepCare Project. Health for All, Target 12, 1998 [<http://www.who.dk/document/e60246.pdf>]

Bech P. Measuring the dimensions of psychological general well-being by the WHO-5. QoL Newsletter 2004; 32: 15-16.

[figure not shown][figure not shown]

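### Psychological health, general quality of life and satisfaction are promised or hypothesised, but no scored, scheduled measure is assigned to them; only the knee-related part of the hypothesis can be tested, through KOOS

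*Protocol*

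**What the plan says.** Section 1.1 makes two statements about psychological health. Of the short-term phase it says: "It provides immediate data regarding how it affects physical function, psychological health, and knee pain". Of the 12-week follow-up phase it says that all 40 participants are "included in this phase, which examines knee pain, physical function, and psychological health".

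Specific objective 3 in section 1.4.2 is "To evaluate patient-centered outcomes, including the impact on daily activities, quality of life, and overall patient satisfaction". Hypotheses 2 and 3 in section 1.5 both end: "These experiences will significantly contribute to improved daily functioning, enhanced quality of life, and overall patient satisfaction compared to those in the control group". They are the same hypothesis printed twice, with the laser abbreviated in one.

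The quantitative outcomes in section 3.1.7 are KOOS, active knee flexion, TUG, NPRS and knee X-ray. WHO-5 and SF-36 come in section 3.2.3, in the qualitative phase. That section says of well-being, experiences and perspectives: "These outcomes will be explored through structured one-on-one interview, which allowing participants to share their subjective experiences and perceptions". It then says: "The interview script is generated based on WHO-5 Well-Being Index and SF-36". Each scale is listed as a numbered measure with psychometric data, SF-36 with score thresholds, and both forms are appended. The WHO-5 appendix explains the scoring: "To obtain a percentage score ranging from 0 to 100, the raw score is multiplied by 4".

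On the interview sample, section 3.2.2 says: "Total of 10 participants from each group will be randomly selected using a computer-generated list". It adds that sampling continues until thematic saturation. Section 3.2.4 specifies thematic analysis.

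**The concern.** A hypothesis of significant superiority over control needs three things: a score, a schedule that includes baseline, and a comparison between the arms. For psychological health, general health-related quality of life and satisfaction, the protocol supplies none of these.

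Two things are at stake. First, a report could say that laser improved well-being or satisfaction over placebo when the only evidence is open interview answers from about half the participants, collected after treatment. Second, the role of WHO-5 and SF-36 is unclear enough that one team member could hand out the forms while another treats them only as source material for the script. A statistical analysis plan cannot repair this later: which forms are given, to whom and when is protocol content, and a form not completed at baseline cannot be recovered.

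**Working it through.** **Step 1. Match each promised construct to a measure.**

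| Construct | Where promised | Scored measure in 3.1.7 | Between-group test |
|---|---|---|---|
| Daily functioning | Hypotheses 2/3; objective 3 | KOOS ADL (17 items, scored separately) | Yes, repeated measures ANOVA (3.1.8) |
| Quality of life, knee-related | Hypotheses 2/3; objective 3 | KOOS Quality of Life (4 items, scored separately) | Yes, as above |
| Quality of life, general | Possible reading of the same wording | None | None |
| Satisfaction | Hypotheses 2/3; objective 3 | None; no instrument named anywhere | None |
| Psychological health | Section 1.1, both quantitative phases | None | None |

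**Step 2. Check whether the interviews fill the gap.** The script in section 3.2.3 has five open questions. They ask participants to look back over the intervention, so there is no baseline. None yields a score. They go to 10 + 10 = 20 of 40 participants, a number that may shift with saturation. Thematic analysis compares themes across interviews; it does not estimate or test a difference between arms. For satisfaction, the nearest question asks whether expectations were met.

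**Step 3. Check whether WHO-5 and SF-36 fill the gap.** Section 3.2.3 treats them in two ways. The numbered listing, SF-36 thresholds and appended forms suggest that the scales are to be completed and scored. The only sentence stating their use makes them the basis of the script. No visit, respondent group, score endpoint or analysis is given. Section 3.2.3 describes them as measures of well-being and health-related quality of life, so neither would cover satisfaction.

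**Step 4. The planned sample size.** The 40 is derived for KOOS from an effect size of 0.3, 90% power, 5% alpha and 20% dropout. It can be reproduced by assuming that 0.3 is Cohen's f for a group-by-time interaction, with m = 2 measurements and correlation rho = 0.5 (the protocol states none of these). Then lambda = f² × N × m / (1 − rho) = 0.09 × 32 × 2 / 0.5 = 11.52, which gives power 0.907 at N = 32, and 32 / 0.8 = 40. Other choices give other totals; with m = 3 and rho = 0.5, N is 26, or 33 after dropout. The total was not sized for the three unmeasured constructs.

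**Step 5. What scoring the forms would buy (context for the fix, not the size of the defect).** Two-sample t-test, two-sided 5%, df = 2n − 2, noncentrality d × √(n/2):

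| n per arm | Detectable d, 80% power | Detectable d, 90% power | Power at d = 0.5 |
|---|---|---|---|
| 10 (interviewees only) | 1.32 | 1.53 | 18.5% |
| 16 (20 × 0.8, after planned dropout) | 1.02 | 1.18 | 28% |
| 20 (all randomised) | 0.91 | 1.05 | 34% |

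These figures come before any gain from baseline adjustment.

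**The case against.** The strongest reply is that the hypothesis is mainly qualitative. Its subject is lived experience and perception, it parallels research question 2 and main objective 2, and the section 3.2 heading places psychological well-being in the interviews. On that view, the word significantly is loose usage and promises no test. This has some force, but the sentence still names a comparison with the control group, and section 1.1 separately assigns psychological health to the quantitative phases in all 40.

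A reader might go further than the documents allow in four ways:

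- **That two of the three hypotheses are untestable.** Hypotheses 2 and 3 are one hypothesis printed twice, and KOOS ADL and KOOS Quality of Life test part of it. The hypothesis says quality of life without calling it generic.
- **That a between-group gain in psychological health is claimed.** The hypotheses do not name it; section 1.1 says only that it is examined and that data on it are provided.
- **That WHO-5 and SF-36 will certainly not be administered.** Section 3.2.3 is ambiguous. What can be said is that no administration or scoring is specified.
- **That the interviewees are hand-picked.** They are drawn at random from a computer-generated list.

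It is also fair to say that the power figures do not measure the defect, since nobody proposes to score open interviews. They also show that scoring the forms in all 40 would leave low power for a medium effect.

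**Conclusion.** The point holds in limited form. Three constructs lack a scored, scheduled measure and a group comparison: psychological health (promised for all 40), satisfaction (hypothesised against control), and general health-related quality of life, if that is what the hypothesis means. Daily functioning and knee-related quality of life are covered by KOOS. The interviews cannot support or refute a comparative claim on any of these.

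This rests on reading the documents side by side, not on a calculation. It assumes that section 3.2.3 means what it states about the scales, with no administration described elsewhere. The primary outcome and its analysis are unaffected. It is still worth correcting, because the fix is cheap and uncollected baseline forms are lost for good.

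**What to change.** **If the team wants to study these constructs quantitatively:** state in section 3.1.7 that WHO-5, and SF-36 if the burden is accepted, is self-completed and scored in all 40 participants at baseline, week 8 and the long-term visit. List them as secondary outcomes analysed with the same between-group model as the others, and keep the interviews descriptive. The cost is 5 items per visit for WHO-5 alone or 5 + 36 = 41 for both, at existing visits and with forms already appended. The downsides are participant burden, more secondary outcomes and limited power. This works only for participants who have not yet passed baseline.

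**If not:** delete psychological health from the descriptions of the all-participant phases in section 1.1. This costs nothing.

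**In either case:**

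- Tie the comparative daily-functioning and quality-of-life hypothesis to the KOOS ADL and Quality of Life subscales.
- Remove satisfaction from the between-group hypothesis, or add a single satisfaction item. WHO-5 and SF-36 would not supply one.
- Delete the duplicate hypothesis.
- State in section 3.2.3 whether the two scales are administered or only inform the script.
- State that the interviews support no between-group inference.

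Apart from an added satisfaction item, these are changes of wording only.

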#### Interview Script

- 1) How has the intervention, specifically the physiotherapy management, impacted your experience with knee osteoarthritis?
- 2) Feel free to discuss any challenges or successes you've encountered during the intervention, and whether your expectations were met.
- 3) Can you describe any noticeable improvements in your knee pain or related issues since the start of the intervention?
- 4) How do you perceive the impact of the intervention on your overall quality of life?
- 5) How would you describe your emotional well-being in relation to your knee osteoarthritis after undergoing the intervention?

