### **1.4 Research Objectives**

#### **1.4.1 Main Objectives**

- 1) To examine the long-term effects of high-intensity laser therapy (HILT) combined with rehabilitation exercise on knee pain, physical function, and disability levels among adults with early knee osteoarthritis (KOA).
- 2) To investigate the lived experiences and perceptions of individuals with early knee osteoarthritis undergoing the combined intervention of HILT and rehabilitation exercise.

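### No interview question names the laser, question 1 narrows to physiotherapy, and question 3 asks only for improvement, so main objective 2 is weakly covered

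*Protocol*

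**What the plan says.** Main objective 2 (Protocol, section 1.4.1) is "To investigate the lived experiences and perceptions of individuals with early knee osteoarthritis undergoing the combined intervention of HILT and rehabilitation exercise". The opening of section 3.2 adds a contrast: the accounts of participants given HILT with exercise are to be compared with those of participants given placebo laser with exercise. Section 3.2.2 plans 10 participants per group and also says that sampling goes on until thematic saturation.

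Section 3.2.1 describes individual interviews "using a structured research questionnaire", asked conversationally so that participants can elaborate. The Interview Script under section 3.2.3 gives all five questions:

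- Question 1, which opens the interview, is "How has the intervention, specifically the physiotherapy management, impacted your experience with knee osteoarthritis".
- Question 2 is an open invitation to speak about good and bad alike: "Feel free to discuss any challenges or successes you've encountered during the intervention, and whether your expectations were met".
- Question 3, the one on symptoms, reads "Can you describe any noticeable improvements in your knee pain or related issues since the start of the intervention".
- Question 4 is about perceived effect on quality of life, and question 5 is about the participant's emotional state once treated. Neither mentions a component of treatment.

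**The concern.** The laser is the only planned difference between the arms, and section 1.2 justifies the qualitative work by the lack of such research on HILT. A reader would expect at least one question to reach the laser. None does by name, and the only component that the script singles out is physiotherapy, which both arms receive. In a structured interview, views on the laser would then appear mainly when a participant volunteers them. Any theme that separates HILT from placebo would rest on those volunteered remarks.

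The second worry is direction. Hypotheses 2 and 3 in section 1.5 predict positive experiences. Question 3 asks for improvements and has no matching prompt for no change or worsening, so it leans towards the predicted answer in both arms.

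**Working it through.** No sample size, power or error rate bears on this point, so the check is a reading of the script item by item against the objective.

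**Inputs.** Main objective 2 (section 1.4.1); the arm contrast (opening of section 3.2); the components of treatment (section 3.1.6); the interview format (section 3.2.1); the number interviewed (section 3.2.2); the five questions (Interview Script).

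**Step 1: what physiotherapy means in the Protocol.** Section 3.1.6 gives both groups individually tailored standard physiotherapy. It uses that label for the knee exercise programme and treats the active or sham laser as an adjunct. On that usage, question 1 points to the shared component.

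**Step 2: the questions side by side.**

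| Question | Names the laser? | Narrowed to one component? | Direction of wording |
|---|---|---|---|
| 1 | No | Yes, physiotherapy | Neutral |
| 2 | No | No | Two-sided: difficulties, successes, expectations |
| 3 | No | No | One-sided: improvements |
| 4 | No | No | Neutral |
| 5 | No | No | Neutral |

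**Step 3: counts.**
- Questions naming the laser: 0 of 5.
- Questions narrowed to the shared component: 1 of 5 (question 1).
- Questions asking only for improvement: 1 of 5 (question 3, which is also the only one on knee symptoms).
- Questions that explicitly invite negative experience: 1 of 5 (question 2).
- Questions neutral in direction: 3 of 5 (questions 1, 4 and 5). As a check, 1 + 1 + 3 = 5.

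**Step 4: what is left to cover the objective.** Questions 2 to 5 (4 of 5) ask about the intervention without narrowing it. Sections 3.2 and 3.2.3 describe the intervention as laser or placebo laser together with exercise, so these four questions can draw out the laser, but none directs the participant to it.

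**Step 5: reach.** The same script serves every interview: 10 + 10 = 20 as planned, or another number if saturation governs.

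**The case against.** The strongest defence is that the objective concerns the combined intervention, not the laser in isolation. Questions 2 to 5 ask about exactly that object, the conversational style lets people elaborate, and the arm contrast comes from comparing the two groups' accounts. This stands in part. It rules out the stronger reading that a reader might infer, namely that the objective cannot be answered or that the interviews collect views on physiotherapy alone. It does not supply a laser prompt. Elaboration follows the questions posed, and improvised probing could differ between interviews.

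A reader might also infer that the script asks only about benefit, or that the hypothesis of positive experience could not fail. The text does not support either inference. Question 2 invites difficulties and unmet expectations, three other questions are neutral, and question 3 can be answered with none.

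A participant may count the laser as physiotherapy. Recruitment is through the Physiotherapy Department, and section 3.1.6 has a laser-trained physiotherapist give the treatment sessions in the HILT group. This is a fair alternative reading, but it makes the qualifier in question 1 ambiguous rather than helpful.

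Silence about the laser might also be defended as protecting blinding. Section 3.1.6 makes the procedure look and sound the same in both arms, so participants already know that they receive a laser procedure, and an identical neutral question reveals no allocation. It could still prompt guessing, which is a reason to control when the interview takes place.

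Finally, specific objective 3 covers patient-centred outcomes, "including the impact on daily activities, quality of life, and overall patient satisfaction", and no question asks about daily activities. The objective is not assigned to the interviews alone, however, and the Knee Injury and Osteoarthritis Outcome Score (KOOS) has a 17-item scale for activities of daily living. That gap is minor.

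**Conclusion.** The point holds in a limited form. The script fits main objective 2 poorly in three specific ways: no question names the laser, question 1 narrows to what in the Protocol's own terms is the shared component, and question 3 is one-sided. The objective is weakly covered, and the lean towards benefit is confined to question 3.

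This affects one of the two main objectives and every interview. It does not touch the randomised comparison, the primary outcome, the sample size or the safety assessment. The conclusion assumes that interviewers keep to the five questions as written, and that physiotherapy in question 1 carries the meaning it has in section 3.1.6. The changes are worth making because they cost little before interviews start and the gap is hard to repair afterwards.

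**What to change.** In the Interview Script:

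- **Question 1:** delete the qualifier about physiotherapy management, so that the question covers the whole intervention.
- **Question 3:** ask what changes, if any, the participant has noticed in the knee, whether better, worse or none.
- **New question:** add one neutral item, worded identically in both arms, such as *How did you find the laser sessions, and what, if anything, did you notice during or after them?*
- **Timing, as a condition of the new question:** hold each interview after that participant's last blinded assessment, so that talk about the laser cannot affect KOOS, the pain rating or the Timed Up and Go test. The text of section 3.2 does not fix the order. If the trial flow chart or Gantt chart already does, this adds nothing.
- **Optional:** mention daily activities in question 4. KOOS already measures them.

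The cost is a short edit to the script, an ethics notification before interviews start, a few more minutes per interview, and the constraint of interviewing after the final assessment.
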